**Other design features**

**Secondary Ids**

*empty*

**Ethics committees**

1

|                         |                                                                                                                                                                                                                                                                                                                                 |
|-------------------------|---------------------------------------------------------------------------------------------------------------------------------------------------------------------------------------------------------------------------------------------------------------------------------------------------------------------------------|
| Ethics committee | 

Name of ethics committee
Ethics committee of Shahid Beheshti University of Medical Sciences

Street address
[name]

City
Tehran

Province
Tehran

Postal code
[name]

 |
|-------------------------|---------------------------------------------------------------------------------------------------------------------------------------------------------------------------------------------------------------------------------------------------------------------------------------------------------------------------------|

|                                          |                             |
|------------------------------------------|-----------------------------|
| Approval date                     | 2023-06-14, 1402/03/24      |
| Ethics committee reference number | IR.SBMU.RETECH.REC.1402.165 |

**Health conditions studied**

1

|                                                |                                     |
|------------------------------------------------|-------------------------------------|
| Description of health condition studied | Total Knee Arthroplasty             |
| ICD-10 code                             | M17.9                               |
| ICD-10 code description                 | Osteoarthritis of knee, unspecified |

Primary outcomes

|   |                       |                                             |
|---|-----------------------|---------------------------------------------|
| 1 |                       |                                             |
|   | Description           | total blood loss                            |
|   | Timepoint             | Before intervention, 24h after intervention |
|   | Method of measurement | amount of Hemoglobin drop                   |

Secondary outcomes

|   |                       |                                                     |
|---|-----------------------|-----------------------------------------------------|
| 1 |                       |                                                     |
|   | Description           | Transfusion rate                                    |
|   | Timepoint             | Before the intervention, 24h after the intervention |
|   | Method of measurement | number of units of blood transfused                 |

Intervention groups

|   |             |                                                                                                                                                                                                                                                                                                                                                                   |
|---|-------------|-------------------------------------------------------------------------------------------------------------------------------------------------------------------------------------------------------------------------------------------------------------------------------------------------------------------------------------------------------------------|
| 1 |             |                                                                                                                                                                                                                                                                                                                                                                   |
|   | Description | Control group: The patients in the control group will receive only normal saline.                                                                                                                                                                                                                                                                                 |
|   | Category    | Treatment - Surgery                                                                                                                                                                                                                                                                                                                                               |
| 2 |             |                                                                                                                                                                                                                                                                                                                                                                   |
|   | Description | Intervention group: The patients in the intervention group will receive the first ascorbic acid dose (1 g in 10 mL) at the beginning of the surgery. Another dose of ascorbic acid (1 g in 10 mL) will be infused during the surgery. After the surgery, an additional dose of ascorbic acid (1 g in 10 mL) will be infused postoperatively during the first 12h. |
|   | Category    | Treatment - Surgery                                                                                                                                                                                                                                                                                                                                               |

Recruitment centers

|   |                    |                                                                                                                                                                                       |

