## Protocol summary

|                                                      |                                                                                                                                                                                                                                                                                                                                                                                                                                                                                                      |
|------------------------------------------------------|------------------------------------------------------------------------------------------------------------------------------------------------------------------------------------------------------------------------------------------------------------------------------------------------------------------------------------------------------------------------------------------------------------------------------------------------------------------------------------------------------|
| Study aim                                     | In this study we are aiming to investigate the effect of the antioxidant agent including ascorbic acid on the amount of hidden blood loss in total knee arthroplasty (TKA).                                                                                                                                                                                                                                                                                                                          |
| Design                                        | A double-blind randomized controlled trial with two parallel groups                                                                                                                                                                                                                                                                                                                                                                                                                                  |

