| Purpose                                | Treatment                                                                                                                                                                                                                                                                                                                                                                                                                                                                                                                                                                                                                                                                                       |
| Inclusion/Exclusion criteria           | 
Inclusion criteria:
Candidates of total knee arthroplasty patients who provide written informed consent to be included in this study
 
Exclusion criteria:
history of thromboembolic events like deep vein thrombosis or pulmonary embolism history of cardiovascular disease like myocardial infarction or atrial fibrillation being in pregnancy or in the lactation period drug abusers or alcoholics severe renal dysfunction severe infection the preoperative hemoglobin less than 10 g/dL diagnosis of inflammatory arthritis like rheumatoid arthritis, pigmented villonodular synovitis and etc clotting disorders including abnormal PT, PTT or INR
 |
| Age                                    | No age limit                                                                                                                                                                                                                                                                                                                                                                                                                                                                                                                                                                                                                                                                                    |

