| Sample size                            | Target sample size: 100                                                                                                                                                                                                                                                                                                                                                                                                                                                                                                                                                                                                                                                                  |
| Randomization (investigator's opinion) | Randomized                                                                                                                                                                                                                                                                                                                                                                                                                                                                                                                                                                                                                                                                                      |
| Randomization description              | In this randomized controlled clinical trial, the patients will be consecutively and alternately (one in between) assigned into two groups in a 1:1 ratio.                                                                                                                                                                                                                                                                                                                                                                                                                                                                                                                                      |

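### The primary outcome, total blood loss, is defined only as a haemoglobin drop, with no account of blood transfused before the 24-hour sample

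*Protocol*

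**What the plan says.** Under Primary outcomes (Protocol, Health conditions studied) the outcome is "total blood loss", the timepoints are "Before intervention, 24h after intervention", and the method of measurement is "amount of Hemoglobin drop". No volume formula, blood-volume estimate or transfusion term appears there or elsewhere in the visible text.

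Under Secondary outcomes, the transfusion rate is measured as "number of units of blood transfused", with timepoints "Before the intervention, 24h after the intervention". The two outcomes share one window, and nothing links them.

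Three entries under General information bear on the point:
- Eligibility excludes "the preoperative hemoglobin less than 10 g/dL" but sets no upper haemoglobin limit and no age limit, and admits both sexes.
- The sample size is given as "Target sample size: 100", at 1:1, with no effect size, SD or power.
- Recruitment status is listed as complete.

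**The concern.** A blood loss is a volume, or a mass of haemoglobin. A haemoglobin drop is a change in concentration. It tracks loss but differs from it in two ways that matter here.

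First, a transfusion between the two samples raises the second value and makes the recorded loss smaller. The protocol expects that transfusions may occur, since it counts them over the same 24 h. If ascorbic acid reduces bleeding and so reduces transfusion, a benefit on the secondary outcome takes away part of the benefit visible on the primary one.

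Second, the same volume lost produces a larger drop in a patient with a small blood volume or a high baseline haemoglobin. That adds between-patient spread unrelated to treatment.

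At stake are the size of the estimated effect, the power of a trial with 50 patients per arm, and whether the result can be reported as blood loss at all.

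**Working it through.** **What can be reproduced.** The target of 100 comes with no design inputs, so it cannot be re-derived. For scale, 50 per arm (two-sided 5%) detects a standardised difference of (1.960 + 0.842) × √(2/50) = 0.56 with 80% power, and (1.960 + 1.282) × √(2/50) = 0.65 with 90% power. Every clinical input below is an assumption; the protocol supplies none.

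**Transfusion, by arithmetic.** Observed difference = transfusion-free difference − (Hb rise per unit) × (mean units in control − mean units in treated).

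- With 0.7 to 1.0 g/dL per unit, a difference of 0.1 units per patient removes 0.07 to 0.10 g/dL. A difference of 0.3 units removes 0.21 to 0.30 g/dL.
- Against an assumed true difference of 0.5 g/dL, these are 14–20% and 42–60%.
- Example at 1 g/dL per unit and 1.5 units per transfused patient: 20% versus 10% transfused removes 0.10 × 1.5 = 0.15 g/dL, and 10% versus 5% removes 0.05 × 1.5 = 0.075 g/dL. With SD 1.0 and 50 per arm, power falls from 0.70 (difference 0.50) to 0.41 (0.35) and 0.56 (0.425) respectively.
- If mean units are equal in the two arms, nothing is removed.

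**Transfusion, by simulation.** There were 400,000 patients per arm, with power then evaluated at 50 per arm. Assumptions: baseline Hb 13 g/dL (SD 1.2, floor 10); loss 1.2 L in control and 1.0 L in treated (SD 0.35); blood volume 4.3 L (SD 0.6); Hb after loss = Hb0 × exp(−V/BV) plus noise of SD 0.3; 1 g/dL rise per unit; all units given before the 24 h sample. Transfusion frequency was varied only to generate a range.

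| Mean units, control / treated | Difference with units added back (g/dL) | Difference as observed (g/dL) | Shrinkage | Power as observed |
|---|---|---|---|---|
| 0 / 0 | 0.473 | 0.473 | 0% | 0.66 |
| 0.012 / 0.005 | 0.475 | 0.468 | 2% | 0.65 |
| 0.091 / 0.045 | 0.478 | 0.431 | 10% | 0.60 |
| 0.363 / 0.215 | 0.474 | 0.326 | 31% | 0.39 |
| 0.927 / 0.640 | 0.475 | 0.188 | 60% | 0.15 |

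The rows agree with the identity; for instance 0.474 − (0.363 − 0.215) = 0.326. With units added back, power stays at 0.66 to 0.67 throughout.

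**Blood volume.** Drop = Hb0 × (1 − exp(−V/BV)). A 1 L loss at baseline 13 g/dL gives 3.23 g/dL when BV is 3.5 L and 2.00 g/dL when it is 6 L. At BV 4.5 L it gives 2.39 g/dL from baseline 12 and 2.79 g/dL from baseline 14. These are contrasts between individuals.

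Between balanced arms without transfusion, adding a blood-volume SD of 0.6 L leaves the mean difference at 0.47 g/dL, raises the SD from 0.92 to 1.00, and lowers power from 0.72 to 0.66. Analysing loss in litres gives power of about 0.81. That last figure uses the simulated true loss, so it is a ceiling for a loss calculated from an estimated blood volume.

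**The case against.** The strongest reply is that the shrinkage is not demonstrated. The protocol gives no transfusion rate or trigger and does not say that units precede the 24 h sample. Excluding low baseline haemoglobin and clotting disorders may make transfusion rare, in which case the table suggests 2% to 10%. This stands. A reader might infer that the measure is known to bias the trial toward no effect, but the documents support only the conditional statement.

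A reader might also infer that ignoring blood volume biases the comparison, the more so because allocation is by alternation. With balanced arms the mean difference is unaffected. Under the assumptions above, chance imbalance at 50 per arm has a standard error of about 0.07 g/dL from blood volume and 0.05 g/dL from baseline haemoglobin, and it can go either way. Simple randomisation would not guarantee balance on these either. Alternation is a separate matter.

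Nor can it be said that a haemoglobin drop does not measure loss. It rises with loss and is an imperfect surrogate for it.

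Finally, the entry is a short registry field, and the drop might be meant as input to a loss formula. That is possible, but the field is where the primary measurement is fixed, and it names no formula. How the primary outcome is measured belongs in the protocol. Adjustment for baseline haemoglobin in the model, by contrast, is ordinary SAP content and is not part of this point.

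**Conclusion.** The point holds in a limited form. As written, the primary measure under-records loss in any patient transfused before the 24 h sample, although the trial records the units needed to correct it. The effect on the treatment comparison is conditional: none if transfusion is absent or equal between arms, about 10% of the difference if it is uncommon, and 30% or more if it is common and unequal. Those figures rest on an assumed rise of 1 g/dL per unit and on assumed losses and transfusion frequencies; nothing in the protocol narrows the range.

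Leaving out blood volume is a matter of precision and labelling rather than of direction. Under the same assumptions, power is about 0.66 for the haemoglobin drop against at most about 0.81 for loss in litres.

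**What to change.** Before any unblinded analysis, define the primary outcome as calculated blood loss in mL. State the blood-volume formula (from height, weight and sex) and the haemoglobin-balance formula, and add the red cells transfused between the two samples. One explicit form is: haemoglobin lost = blood volume × (Hb before − Hb at 24 h) + haemoglobin transfused, divided by baseline Hb to give a volume. Naming the form matters. For the 1 L loss above (BV 4.5 L, baseline 12), this linear form returns 4.5 × 2.39/12 = 0.90 L, whereas the exponential model returns 1 L.

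The visible text does not say that height and weight are collected. If they cannot be retrieved from charts, use the haemoglobin drop with a stated add-back per unit transfused before the 24 h sample, and call it haemoglobin drop rather than total blood loss.

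The work is one formula and a chart search; no new patients or samples are needed. The costs are reliance on a blood-volume formula and on an assumed haemoglobin content per unit. Because recruitment is listed as complete, document the change as made before unblinding and report the raw haemoglobin drop alongside it.

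This does not settle a neighbouring mismatch: the title and aim concern hidden loss, while the outcome is total loss. A calculated total does not separate the two, so the protocol should also say which is meant.

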**Sponsors / Funding sources**

1

**Sponsor**

**Name of organization / entity**

Shahid Beheshti University of Medical Sciences

**Grant name**

**Grant code / Reference number**

**Is the source of funding the  
same sponsor  
organization/entity?**

Yes

|                                                   |                                                |
|---------------------------------------------------|------------------------------------------------|
| Title of funding source                    | Shahid Beheshti University of Medical Sciences |
| Proportion provided by this source         | 100                                            |
| Public or private sector                   | Public                                         |
| Domestic or foreign origin                 | Domestic                                       |
| Category of foreign source of funding      | empty                                   |
| Country of origin                          |                                                |
| Type of organization providing the funding | Academic                                       |

## Sharing plan

|                                                             |                                                                                             |
|-------------------------------------------------------------|---------------------------------------------------------------------------------------------|
| Deidentified Individual Participant Data Set (IPD)   | Yes - There is a plan to make this available                                                |
| Study Protocol                                       | Undecided - It is not yet known if there will be a plan to make this available              |
| Statistical Analysis Plan                            | Undecided - It is not yet known if there will be a plan to make this available              |
| Informed Consent Form                                | Undecided - It is not yet known if there will be a plan to make this available              |
| Clinical Study Report                                | Yes - There is a plan to make this available                                                |
| Analytic Code                                        | Undecided - It is not yet known if there will be a plan to make this available              |
| Data Dictionary                                      | Not applicable                                                                              |
| Title and more details about the data/document       | Information about the main outcome can be shared after making the individuals undetectable. |
| When the data will become available and for how long | Access will be granted 6 months after the results of the study are published.               |
| To whom data/document is available                   | Researchers and medical specialist                                                          |
| Under which criteria data/document could be used     | based on the Ministry of Health and Medical Education criteria for clinical trials          |
| From where data/document is obtainable               | Orthopedic department of Shahid Beheshti Medical University                                 |

**What processes are involved  
for a request to access  
data/document**

The data will be provided after reviewing the researcher's request and providing sufficient documentation of their research and the reason for using the data.

---

